#### Non-dietary data collection

In phases 1 and 2, in addition to dietary intake, socioeconomic and demographic data such as gender (sex), age, education, and level of physical activity will be collected using a structured questionnaire from the clinical patients. The blood pressure and anthropometric data (such as weight and height) will be measured using a standard procedure from each clinical patient, and the average will be calculated and used. Body mass index (BMI) will be calculated using weight in kilograms by height in meters squared. Hypertension will be defined as SBP ≥ 140mm Hg and DBP ≥ 90mm Hg or on antihypertension medication [34].

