### Outcomes

*Primary outcome measures*. The primary outcome of this study is to develop and validate a short dietary screening tool (FFQ) for potential implementation in the Nigerian healthcare system for clinical practice, pending the results of this rigorous evaluation. While this tool alone will not eliminate unhealthy diet or hypertension risk, it can help prioritise diet as a practical means of risk assessment and prevention of hypertension in Nigeria if found to be valid, feasible and acceptable. This analysis of the result of the study will focus on descriptive data related to feasibility, validity, reproducibility and qualitative perceptions of the FFQ among the study population. However, limitations exist in the generalizability of the findings beyond Nigeria, as the tool was designed specifically for cultural, lifestyle and dietary habits within this population. Additional research would be needed to adapt and validate the FFQ for other countries and settings. While the study aims to positively impact clinical practice in Nigeria, we acknowledge these limitations upfront and will interpret results accordingly if the FFQ performs well in our evaluations.

*Secondary outcome measures*. Secondary outcomes will evaluate the agreement between FFQ and 24-hour dietary recalls (24HR) in assessing dietary intake, using correlation coefficients to establish consistency between methods. Additionally, we seek to explore the association between FFQ scores and hypertension risk, quantifying the odds ratio that reflects the odds of hypertension about the FFQ scores. Furthermore, we will assess the acceptability of the FFQ through participant-reported feedback, providing insights into the practicality and user-friendliness of the tool.

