### Participant timeline

The participant timeline and schedule of enrolment, interventions, assessments, and visits for participants are outlined in **Fig 1** in accordance with SPIRIT guidelines. During Phase 1, a one-month recruitment period will be initiated to identify clinical patients meeting the eligibility criteria. These patients will be approached for informed consent and subsequently categorised into two groups based on their history of hypertension. Participants will undergo comprehensive baseline assessments in the initial week of their clinical appointments. These assessments will encompass the administration of the Food Frequency Questionnaire (FFQ) and the First 24-hour dietary recall (24HR).

The participant’s blood pressure and essential anthropometric measurements, including height and weight, will also be recorded. Moreover, demographic and health status information will be collected to overview the participants’ profiles comprehensively. A second 24-hour dietary recall assessment will be conducted in the subsequent weeks, followed by a final set of assessments in the third-week post-allocation. These final assessments will include the administration of the second FFQ, the third 24-hour dietary recall (24HR), and recording blood pressure, height, and weight measurements.

Phase 2 of the study will involve participants who have provided informed consent. Over four weeks, participants will undergo assessments during their clinical appointments. Central to this phase is the refined FFQ-based dietary intake evaluation, designed to capture detailed information on participants’ dietary habits. Simultaneously, height and weight measurements will be taken to ensure accurate and up-to-date anthropometric data. Additionally, relevant demographic and health status information will continue to be collected, allowing for a comprehensive understanding of participants’ backgrounds and overall health profiles. This phase provides a detailed and in-depth analysis of participants’ dietary habits and their potential correlation with hypertension status.

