### Assignment of interventions

Participants in this study will be allocated into non-hypertensive and hypertensive groups based on their history of hypertension, as illustrated in **Fig 2**. Allocation will be conducted following predefined criteria and without randomisation. The implementation of group allocation will be carried out by the primary investigator based on the predetermined criteria. Participants will not be informed of their assigned group during their respective clinic appointments. Allocation will be conducted in a standardised and systematic manner to uphold the integrity of the study.

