#### Assessment of the FFQ score and hypertension risk

The refined FFQ will be administered to the clinical patients (n = 50) to assess their dietary habits. Individual FFQ scores will be calculated for each clinical patient from their FFQs. A logistic regression will be performed between FFQ scores and hypertension risk (blood pressure), with a correlation coefficient (r) of around 0.5, suggesting a moderate to strong association. The odds ratio will be calculated to quantify the strength of the association between the FFQ score and hypertension.

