Dietary intake according to the 27-item FFQ will be used to develop an FFQ score based on associations between individual foods and blood pressure using correlation and regression analysis. The result of the regression models will inform the weighting and scoring assignment for each food item in the FFQ. Following the assignment of scores for each individual food item, an aggregation process will be undertaken to obtain an overall dietary score for each participant. The association between the FFQ score and blood pressure will be evaluated using regression analysis, allowing for a robust evaluation of the scoring system’s predictive validity and adjusting for potential confounders, such as age, sex, BMI, physical activity, and socioeconomic status.

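### The hypertension definition requires both pressures to be raised, so untreated patients with one raised pressure count as non-hypertensive, and it is not reconciled with the grouping by history

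*Protocol article*

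**What the plan says.** Non-dietary data collection gives the only rule that turns measurements into a hypertension status: "Hypertension will be defined as SBP ≥ 140mm Hg and DBP ≥ 90mm Hg or on antihypertension medication". No other section gives a rule under which either pressure alone is enough.

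The groups are formed differently. Under Assignment of interventions, participants are "allocated into non-hypertensive and hypertensive groups based on their history of hypertension"; under Participant timeline, Phase 1 patients are "categorised into two groups based on their history of hypertension". Neither section mentions a blood pressure cut-off or medication. Assignment of interventions adds "Allocation will be conducted following predefined criteria and without randomisation", but does not state those criteria or refer to the definition.

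Binary hypertension is the outcome of a named secondary analysis. Outcomes describes "quantifying the odds ratio that reflects the odds of hypertension about the FFQ scores", and the Phase 2 section on FFQ score and hypertension risk says "The odds ratio will be calculated to quantify the strength of the association between the FFQ score and hypertension", in 50 patients. That section calls the model logistic but puts blood pressure in brackets after hypertension risk. It does not say whether the outcome is the measured status or the history group.

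Other parts use blood pressure as a continuous measure. Study objectives bases the scoring system on it, and Statistical analysis says "The association between the FFQ score and blood pressure will be evaluated using regression analysis".

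**The concern.** There are two linked problems. First, read literally, the definition places an untreated patient with one pressure above the plan's own cut-off among the non-hypertensives. An analyst coding the variable from the text would do exactly that, and nothing elsewhere corrects it. Second, history and measured status are different rules, and the text does not say which one decides who is a case in the logistic model.

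At stake is the odds ratio, one of the ways in which the FFQ score is to be validated in Phase 2. With only 50 patients, moving a handful between cases and controls changes the comparison. If the case definition is settled only after the data are seen, it becomes a post hoc choice.

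**Working it through.** **Step 1. Apply the rules as written.** Here A is SBP ≥ 140, B is DBP ≥ 90 and M is on medication.

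| Patient | (A and B) or M, as written | A or B or M | History rule |
|---|---|---|---|
| 150/85, untreated, no history | no | yes | no |
| 135/95, untreated, no history | no | yes | no |
| 150/95, untreated, no history | yes | yes | no |
| 150/85, untreated, history | no | yes | yes |
| 135/85, untreated, history | no | no | yes |
| 135/85, treated, history | yes | yes | yes |

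Rows 1, 2 and 4 show the effect of *and*. Rows 3 to 5 show the written definition and the history rule giving opposite answers. The other possible parsing, A and (B or M), gives the same result as the written rule for every untreated patient, so the first problem does not depend on how the sentence is parsed.

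**Step 2. How many untreated patients are affected.** The plan has no figure to reproduce here: it gives no blood pressure distribution and no treated share. The inputs below are assumptions: bivariate normal pressures in untreated patients, with mean, SD and SBP–DBP correlation r as shown.

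- Patients changing status = P(either) − P(both).
- Share of raised-pressure patients labelled non-cases = [P(either) − P(both)] / P(either).
- Share of non-cases with a raised pressure = [P(either) − P(both)] / [1 − P(both)].

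| Mean; SD; r | P(either) | P(both) | Difference | Labelled non-cases | Non-cases with a raised value |
|---|---|---|---|---|---|
| 130/80; 18/11; 0.7 | 0.340 | 0.131 | 0.209 | 0.209/0.340 = 61% | 0.209/0.869 = 24% |
| 135/83; 20/12; 0.7 | 0.466 | 0.215 | 0.251 | 0.251/0.466 = 54% | 0.251/0.785 = 32% |
| 125/78; 16/10; 0.6 | 0.228 | 0.061 | 0.167 | 0.167/0.228 = 73% | 0.167/0.939 = 18% |

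If none of 50 patients is treated, 50 × 0.167 to 50 × 0.251 gives about 8 to 13 patients changing status. If 25 are treated, 25 × 0.167 to 25 × 0.251 gives about 4 to 6. A second assumed grid (means 125/78 to 140/86, SDs 18/11 to 20/12, r 0.6 to 0.8) gives 14–31% of untreated patients changing status, and 41–71% of those with any raised pressure labelled non-cases.

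**Step 3. What happens to the odds ratio.** A standardised FFQ score was added to the three distributions above, with assumed correlations with SBP/DBP of 0.3/0.3, 0.5/0.5, 0.5/0.2 and 0.2/0.5: 12 runs, nobody treated. Examples of the odds ratio per SD of score:

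| Scenario | Either | Both |
|---|---|---|
| 130/80; 0.3/0.3 | 1.72 | 1.85 |
| 125/78; 0.3/0.3 | 1.78 | 2.01 |
| 130/80; 0.5/0.2 | 2.17 | 1.89 |
| 125/78; 0.5/0.2 | 2.18 | 2.16 |

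Over the 12 runs the odds ratio was larger under *both* in 9, about equal in 1 and smaller in 2. The expected z at n = 50 fell in 10 of 12, for example from about 2.6 to 2.2 (130/80; 0.5/0.5).

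**Step 4. Which analyses are reached.** The odds ratio in Outcomes and in the Phase 2 section is reached. The weights in Development of FFQ score are reached only if the outcome there is binary. The blood pressure regressions, FFQ–24HR agreement, reproducibility, feasibility, acceptability and the sample size are not.

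**The case against.** The strongest reply is that this is a probable one-word slip affecting one secondary outcome, and that several larger conclusions do not follow. Much of that stands.

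- **Bias toward no association.** A reader might infer that mixing raised-pressure patients into the controls must dilute the odds ratio. Step 3 shows otherwise: the stricter rule picks out more severe cases, and the odds ratio was more often larger than smaller.
- **Distorted food weights.** A reader might infer that the definition drives the score, because Development of FFQ score regresses food tertiles on hypertension. But Study objectives and Statistical analysis base the score on blood pressure as a continuous measure, which no cut-off affects.
- **Conflict with the Introduction.** Its description of hypertension as sustained high blood pressure sets no threshold and no either/both rule, so the definition does not contradict it.
- **Outright contradiction with the history grouping.** The unstated predefined criteria could include the measured definition, and a condensed article may leave them to the full protocol. This is an unreconciled difference, not an explicit contradiction.
- **Size.** The percentages apply to untreated patients only. On the natural parsing a treated patient is a case whichever conjunction is used, and an outpatient clinic may contribute many such patients.

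What the reply does not remove is the literal definition. It is the only one given, and followed as written it codes a patient with one clearly raised pressure as a control.

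**Conclusion.** The definition is wrong as written and should be corrected before analysis. That untreated patients with exactly one raised pressure become non-cases follows from the text alone. So does the possibility that history and measured status disagree, together with the silence on which of them the logistic model uses.

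The size rests on assumed distributions: 54–73% of untreated patients with any raised pressure, or about 8–13 of 50 with nobody treated and about half that with half treated. The supported harm is misclassification, fewer cases and usually lower precision.

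The precision result comes from runs with nobody treated and should not be carried over to a heavily treated sample. With 25 treated, the 130/80 scenario gives 25 + 25 × 0.340 = 33.5 cases under *either* and 25 + 25 × 0.131 = 28.3 under *both*, so scarcity of cases is then no longer the limit. The misclassification remains. The direction of any change in the odds ratio is not determined.

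**What to change.** In the analysis variable, replace *and* with *or* between the two thresholds: SBP ≥ 140 mmHg or DBP ≥ 90 mmHg or on antihypertensive medication. Add a sentence that reconciles Participant timeline, Assignment of interventions, the Phase 2 section and Non-dietary data collection: this one status is both the outcome of the logistic regression and the hypertensive/non-hypertensive grouping in tables, with history reported as a descriptive variable. Development of FFQ score should also say whether its outcome is this status or continuous blood pressure.

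The cost is one word and a sentence or two. Blood pressure is already to be measured in both phases and medication is already part of the definition, so no new data are needed. The change concerns an analysis variable only, not patient management. It should be made before outcome data are examined.

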### Data management

Data management, confidentiality, and access in this study will adhere to stringent security measures. All data collected in physical format (such as Questionnaires, including the primary eligibility screening questionnaire, health questionnaires, and Food Frequency Questionnaires (FFQs)) utilised during participant visits will be digitised through scanning. Both electronic and physical copies will be retained, with the latter securely stored within a locked cabinet in the principal investigator’s secure office.

### Statistical analysis

Statistical analyses will be conducted using R programming language version 4.3.0 [35] with significance level set at p<0.05. Descriptive statistics will be used to analyse categorical and continuous variables. Categorical demographic variables will be analysed using frequency distribution, while continuous demographic variables will be summarised as mean and standard deviation for normally distributed variables and median and interquartile range (IQR) for non-normally distributed variables. As the frequencies of food groups are not normally distributed, differences in frequencies between the two FFQs (FFQ1 vs. FFQ2) and between the two methods (24 HR vs. FFQ2) in phase 1 will be tested using Wilcoxon’s signed-rank test.

Feasibility and acceptability will be assessed through descriptive analyses, including means and 95% confidence intervals (CI), qualitative feedback, and content analysis of indicators related to the process (e.g., proportion interested, started, completed FFQ) and resource (e.g., time to complete and review, rated performance, and practicality).

The West African Food Composition Table will be used to calculate the nutrient content (macronutrients such as energy, carbohydrates or sugar, proteins, fats, and fibre and minerals such as sodium and potassium) of the foods reported in both the FFQ and 24HR. The mean and distribution of nutrient intakes obtained from the FFQ and 24HR will be calculated, and a comparison will be made to assess the differences using the Wilcoxon signed-rank test. Pearson correlations will be used to calculate the correlation coefficients between the FFQ and 24HR for each nutrient to assess the agreement between the FFQs and 24HR and the reproducibility of the FFQs. Additionally, the agreement between the FFQ and the average of three 24-hour dietary recalls will be estimated using Intraclass Correlation Coefficient (ICC), de-attenuation of the correlation coefficients, or quintile cross-classification analysis and the Bland-Altman plots will be used to visualise the agreement between the recalls and FFQ [36–38].

Dietary intake according to the 27-item FFQ will be used to develop an FFQ score based on associations between individual foods and blood pressure using correlation and regression analysis. The result of the regression models will inform the weighting and scoring assignment for each food item in the FFQ. Following the assignment of scores for each individual food item, an aggregation process will be undertaken to obtain an overall dietary score for each participant. The association between the FFQ score and blood pressure will be evaluated using regression analysis, allowing for a robust evaluation of the scoring system’s predictive validity and adjusting for potential confounders, such as age, sex, BMI, physical activity, and socioeconomic status.

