### Sample size and sampling technique

The targeted sample size for this study was determined by previous studies evaluating the agreement between food frequency questionnaires (FFQs) and 24-hour dietary recalls. These studies have found correlation coefficients (r) ranging from 0.3 to o.7, indicating moderate to strong agreement between the two dietary assessment methods [23–26]. Based on this evidence, a modest correlation coefficient of *r* = 0.5 is considered a good indicator of validity for determining the sample size needed to evaluate the agreement between our clinical FFQ and 24-hour recall [27]. Using G*Power software [28], a priori sample size calculation was conducted for a two-tailed correlation analysis with statistical power = 0.8, alpha = 0.05, and r = 0.5. The analysis indicated that a minimum of 29 participants would be needed to detect a significant correlation between the FFQ and recall measures.

In addition, recent evidence suggests that a sample of approximately 13 participants is sufficient to reach saturation in qualitative studies with a small number of clear objectives (*See Section 3*.*4*.*2*: *Feasibility assessment of FFQ*) [29]. Therefore, the planned sample of 29 participants will be sufficiently powered to evaluate the qualitative evidence and feedback. Nonetheless, to account for an anticipated dropout rate of 20% as well as to accommodate any potential missing/incomplete data, the target sample size will be increased to 50 participants (**Fig 2**) [30, 31]. Furthermore, 25 healthcare professionals consisting of nurses, dietitians, and clinicians at RSUTH will be purposely recruited to provide qualitative feedback on the food frequency questionnaire.

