#### Validation and reproducibility of the FFQ

The FFQ will be administered to clinical patients (*n* = 50) twice (i.e., first and third visits) to quantify the intake of food items. Additionally, an inconsecutive three (3) repeated 24HR, including two weekdays and one weekend day, will be used to collect dietary information from the clinical patients for the past 24 hours using the multiple-pass method [21, 22] at the time of visits and intervals between the two FFQs administrations (**Fig 1**). The reproducibility of the FFQ will be assessed by measuring the level of agreement between the two administrations of the FFQ. Furthermore, the validation will be assessed by evaluating the agreement level between the FFQ and the average of the three 24-hour recalls [32, 33]. Healthcare professionals are not involved in the patient FFQ validation stage.

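### For food-group frequencies, FFQ reproducibility is examined only by a Wilcoxon test of no difference, which cannot measure the agreement the protocol sets as its aim

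*Protocol article*

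**What the plan says.** Under Validation and reproducibility of the FFQ, the protocol article sets the aim: "The reproducibility of the FFQ will be assessed by measuring the level of agreement between the two administrations of the FFQ". Fifty patients complete the FFQ twice, and the Outcomes section lists reproducibility among the subjects of the primary-outcome analysis.

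The Statistical analysis section gives the methods:

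- **Food-group frequencies.** Wilcoxon's signed-rank test is applied to "differences in frequencies between the two FFQs (FFQ1 vs. FFQ2) and between the two methods (24 HR vs. FFQ2) in phase 1". The general significance level is p<0.05. No acceptable difference, interval or agreement statistic is attached to the FFQ1–FFQ2 comparison.
- **Nutrients.** FFQ and recall intakes are set against each other: "a comparison will be made to assess the differences using the Wilcoxon signed-rank test". Pearson correlations, specified per nutrient, serve both FFQ–recall agreement and FFQ reproducibility.
- **FFQ against the mean of the three recalls.** ICC, de-attenuated correlation or quintile cross-classification are listed, with Bland-Altman plots. This sentence is not expressly limited to nutrients.

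The Discussion takes a strong ICC and correlations over 0.4 as the signs of a reliable tool, and mentions ICC in connection with reproducibility as well as validity.

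**The concern.** Agreement and absence of a significant shift are different properties. The signed-rank test looks only at whether the paired differences are centred on zero. Two administrations can disagree widely for individual patients and still show no net shift. A real shift can also go undetected because the study is small.

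The other planned analyses do not fill this gap for FFQ1 against FFQ2. The Pearson correlations are for nutrients, and adding a constant to one administration leaves a Pearson correlation unchanged. ICC, cross-classification and Bland-Altman are written for the comparison with recalls.

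Food-group frequencies matter because the score is built from tertiles of them (Development of FFQ score). If tertile cut-points from the test group are carried forward, a systematic change in reporting moves patients across them. A reproducibility statement for these items should therefore rest on a measure that can show both shift and scatter.

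**Working it through.** **1. The plan's own sample size.** The calculation is for a "two-tailed correlation analysis with statistical power = 0.8, alpha = 0.05, and r = 0.5", and concludes that "a minimum of 29 participants would be needed to detect a significant correlation between the FFQ and recall measures". By Fisher's z:

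n = ((1.960 + 0.842)/atanh(0.5))² + 3 = 29.01.

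Simulated power of the correlation test at n = 29 is 0.815. The stated 29 is reproduced. It was set for a correlation, not for a shift between two administrations.

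**2. Pairs available.** The target is 50 patients, "to account for an anticipated dropout rate of 20% as well as to accommodate any potential missing/incomplete data". At 20% loss, 50 × 0.80 = 40 pairs. The range used below is 40 to 50.

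**3. Does the test respond to agreement?** Five-category responses were simulated with no shift (assumed scores 0, 1.5, 4, 7 and 14 per week). For a frequently eaten food the rejection rate was 0.04–0.05 at latent test-retest correlations of 0.3, 0.5 and 0.7 alike. The test gives the same answer for poor and for good repeatability.

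**4. Power against a shift.** Assumptions: two-sided 5% (the article does not state sidedness for this test); CV of food-group frequency 0.6–1.2; within-pair correlation r 0.3–0.7. The article gives neither CV nor r for repeated FFQs. The 0.3–0.7 it cites is for FFQ against recalls and is borrowed here as a range.

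SD of the difference ÷ mean = CV × √(2(1 − r)). At CV 1.0 and r 0.5 this is 1.0 × √1.0 = 1.0, so a 25% shift is 0.25 SD of the difference. Power comes from the paired noncentral t with n multiplied by 3/π, the signed-rank test's relative efficiency. At n = 40 the effective n is 38.2 and the noncentrality is 0.25 × √38.2 = 1.55.

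| Shift (CV 1.0, r 0.5) | Power, n = 40 | Power, n = 50 | Non-significant |
|---|---|---|---|
| 25% of mean | 0.32 | 0.39 | 68% / 61% |
| 40% of mean | 0.67 | 0.77 | 33% / 23% |

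Direct simulation of the test on a continuous scale, with a shift of 0.25 of the between-person SD, gave 67% and 60% non-significant at r = 0.5, and 49% and 41% at r = 0.7.

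**5. Sensitivity.** At n = 40, over the whole CV and r range, power for a 25% shift runs from 0.18 (CV 1.2, r 0.3) to 0.90 (CV 0.6, r 0.7). For a 40% shift it runs from 0.40 to 1.00. The five-category simulation at n = 40, r 0.5 gave:

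| Food type (assumed) | CV | Power, 25% | Power, 40% |
|---|---|---|---|
| Rarely eaten | 1.4 | 0.15 | 0.29 |
| Mid-frequency | 0.96 | 0.30 | 0.62 |
| Frequent | 0.76 | 0.44 | 0.82 |

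**6. What an interval would show.** With SD of the difference equal to the mean, the approximate half-width of a 95% interval for the mean difference is 2.02/√40 = 0.32 of the mean at n = 40 and 2.01/√50 = 0.28 at n = 50. A p-value alone hides this imprecision.

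**The case against.** Three stronger readings are tempting, and the document does not support them.

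- **A reader might infer that all agreement in the study rests on a test of no difference.** It does not. ICC, cross-classification and Bland-Altman are planned for FFQ against recalls and are not expressly confined to nutrients.
- **A reader might infer that the plan will treat p>0.05 as agreement.** Nothing says so. The stated yardsticks are ICC and correlations above 0.4. What remains is that, for food-group reproducibility, the Statistical analysis section attaches neither yardstick to FFQ1 against FFQ2.
- **A reader might infer that shifts up to 40% would usually be missed.** Under CV 1.0 and r 0.5 a 40% shift is usually detected. It is usually missed for rarely eaten, highly variable foods, or where CV is high and correlation low.

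It is also fair to ask whether a 25% shift matters. Take category proportions of 0.20, 0.25, 0.25, 0.20 and 0.10 with the scores above. The mean is 0.375 + 1.0 + 1.4 + 1.4 = 4.18 per week, and 25% of it is 1.04, less than the smallest step of 1.5. A tolerance of one frequency step would accept it. A uniform shift also largely preserves ranking within one administration, so the harm to a tertile score depends on whether cut-points are carried over.

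Finally, item-level statistics may stand in an analysis plan that is not shown. That limits the weight of the point. It does not remove it, because the article does name a method for this comparison, and that method does not match the aim.

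**Conclusion.** The point holds in a narrow form. For FFQ1 against FFQ2 food-group frequencies, the one analysis named cannot measure the agreement that defines reproducibility, whatever the sample size. At 40 to 50 pairs its non-significance is also weak evidence against a shift: about 60–68% of studies would miss a 25% shift at CV near 1 and r near 0.5. That percentage is illustrative. It rests on a CV and a correlation that the article does not supply, and power at n = 40 could be as low as 0.18 or as high as 0.90. The mismatch between aim and method does not depend on these assumptions. It is worth correcting before analysis, and it does not call the study design or the validation against recalls into question.

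**What to change.** In the Statistical analysis section, for each food group:

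- report the FFQ1–FFQ2 difference with a 95% confidence interval;
- add an agreement statistic suited to the five ordered response categories, such as weighted kappa, or an ICC with limits of agreement (an absolute-agreement ICC, since a consistency form ignores a shift);
- base the food-group reproducibility conclusion on these results;
- keep the Wilcoxon test as descriptive, and state that a non-significant result is not evidence of agreement.

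Any tolerance is for the sponsor to set in advance. A formal equivalence test need not be required. With two one-sided 5% tests, 80% power, no true difference and SD of the difference equal to the mean, a ±25% margin needs (2.9264/0.25)² = 137.02, so 138 pairs, and ±40% needs (2.9264/0.40)² = 53.5, so 54. With that ratio at 0.8 the figures are about 88 and 35. At 40 to 50 pairs a tight margin would leave many items undecided.

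The cost is a few lines of wording and slightly more analysis of data already planned. Some food groups will be reported as imprecise or inconclusive.
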